### **Power and sample size**

For the sample size calculation in CRISTAL, we used an estimated overall event rate of 2% (based on the current available literature) [18, 19], a non-inferiority margin of 1% (based on clinician opinion and a recent randomised controlled trial) [12], i.e., an event rate of 2.5% for aspirin and 1.5% for LMWH, a power of 90% and a one-sided significance level of 0.025. For an individual randomised trial, this yields a sample size of 4,117 per treatment group or a total of 8,234 patients. For a cluster-randomised crossover trial with an intracluster correlation of 0.01, an interperiod correlation of 0.008 and 31 clusters, the required sample

size is 11,160 patients, or 180 patients per arm for each cluster [20, 21]. However, due to the uncertainty surrounding the event rate and intracluster and interperiod correlations, loss to follow-up, uneven recruitment rates leading to unequal cluster sizes or clusters dropping out of the study, we aimed to register 251 patients eligible for the primary objective of the study, providing a total of 15,562 patients. This figure allowed for a maximum 27% reduction in the above sample size calculation [15], however, actual loss to follow-up was expected to be less than this.

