### 3.9. Sample size

A recent large cohort study of 1900 THA and TKA patients from 19 institutions across Australia showed an incidence of symptomatic VTE within 90 days of THA and TKA of 2.6% (manuscript under preparation). A recent randomised trial of aspirin versus rivaroxaban used a minimum clinically important difference of 1%, based on a survey of thromboembolism experts and orthopaedic surgeons.

For the sample size calculation in the CRISTAL study, we used an estimated overall event rate of 2% (a conservative estimate based on the recent Australian cohort study and the current available literature), the same non-inferiority margin of 1% from the recent randomised controlled trial (for aspirin compared to LMWH, 2.5% for aspirin and 1.5% for LMWH), a power of 90% and a one-sided significance level of 0.025. For an individual randomised trial, this yields a sample size of 4,117 per treatment group or a total of 8,234 patients. For a cluster randomised crossover trial, the sample size must account for correlations within clusters during the same time period (intracluster correlation) and between study periods in the same cluster (interperiod correlation). Assuming an intracluster correlation of 0.01, an interperiod correlation of 0.008 and 31 clusters, the sample size required increases to 11,160 patients. From each cluster, we will aim to recruit minimum of 251 registered patients from each group (a total of 15,562 patients), which will allow a 27% loss to follow-up.

Due to uncertainty around the exact event rate and to allow for a smaller non-inferiority margin, we have constructed a sample-size table (Table 1) to demonstrate that the trial will be adequately powered using a non-inferiority margin of 1%, for an event rate up to 3% at 80% power and for an event rate up to 2% at 90% power, provided that loss to follow-up is less than 17%. As a secondary measure, after 1,000 patients have completed the 90-day follow-up, we will obtain a preliminary symptomatic VTE rate for the whole sample and a loss to follow-up rate (without performing any comparative statistical analyses and maintaining blinding) to determine whether the estimates for the primary event rate (2%) and loss to follow-up rate (27%) are accurate and adjust the sample size accordingly if the primary event rate is greater than 3%, whilst accounting for loss to follow-up.

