## MAIN ANALYSES

The main analyses will include the primary and secondary outcomes for registered patients eligible to receive the study drug undergoing THA or TKA for a diagnosis of OA (population 1). In addition, the primary and secondary outcomes will be analysed for populations 2, 3 and 4. Mortality will also be analysed for population 5 (see “Additional analyses” below).

For the primary outcome, the analysis will test the between-group difference of cases developing a symptomatic VTE within 90 days for non-inferiority of aspirin at a margin of 1%. Cluster summary methods will be used to estimate the treatment effect using cluster level differences. These have been shown to be appropriate for cluster-randomised crossover trials with rare outcomes, and the intracluster and interperiod correlation coefficients expected in this trial. The crossover difference per cluster is the mean outcome for the intervention period minus the mean outcome for the control period. In a linear regression of cluster differences on treatment sequence, the treatment effect estimate is the intercept. To account for potential unequal cluster sizes, a cluster size weighted estimator will be used with harmonic mean weights of the number of patients in the two periods, which was the same method used in the interim analyses for incomplete crossover [25, 26]. Treatment effects will be presented as absolute risk differences and 95% confidence intervals will be examined to determine whether the non-inferiority margin has been met and whether superiority of one drug can be concluded. The primary outcome will be presented in Table 3 and Figure 4 will be used to demonstrate whether the non-inferiority margin has been met for the population 1 [30].

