The secondary outcomes will investigate non-VTE complications (death, re-operation, readmission and major bleeding events) within 90 days, and reoperation and patient-related pain and function at 6 months (OHS, OKS, EQ-5D and EQ-VAS). Cluster summary methods will be used within an intention-to treat approach. For binary outcomes, the cluster mean per period will be the proportion of patients who had the outcome, while for continuous outcomes such as pain score, the cluster mean will be the mean outcome. Treatment effects will be presented as absolute risk differences and 95% confidence intervals to determine if one treatment is superior to the alternative. Results for the secondary outcomes in population 1 will be presented in tabular form (Table 3) and results for the primary and secondary outcomes in populations 2, 3 and 4 in Table 4.

Due to the early stopping of the trial, final analyses of the primary and secondary outcomes will use the same composite method as the interim analyses which accounts for clusters with incomplete as well as no crossover, with 95% confidence intervals. No bias is expected from early stopping if the patients included in the trial are not systematically different from later patients who would have been included after the trial was stopped. Our composite analysis method accounts for clusters which either had incomplete crossover and or did not crossover. However, the lower sample size and unequal cluster sizes decreases the precision of the outcome estimates. Since we used cluster weighted estimates to account for unequal cluster sizes and increased the initial sample size by 27% above the minimum required, the loss of precision will be mitigated. The trial was stopped based on the Haybittle-Peto

boundary of 0.001, so we anticipate the final analysis using 95% confidence intervals will have sufficient power.

**Table 3.** Outcomes for population 1

| Outcome                                            | LMWH Allocation
(n = X) | Aspirin Allocation
(n = X) | Absolute Risk Difference | 95% Confidence Interval | p-value |
|----------------------------------------------------|----------------------------|-------------------------------|--------------------------|-------------------------|---------|
| Any Venous thromboembolism                  | n (%)                      | n (%)                         | X                        | X – X                   |         |

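### The sample size uses normal quantiles, but the hospital-level regression it was sized for has 29 residual degrees of freedom; the stated power and loss tolerances are modestly too favourable, and a surplus of 39% is reported as 27%.

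*Supplement*

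**What the plan says.** The final SAP (Power and sample size) takes "an event rate of 2.5% for aspirin and 1.5% for LMWH, a power of 90% and a one-sided significance level of 0.025", with a 1% margin. For individual randomisation, "this yields a sample size of 4,117 per treatment group or a total of 8,234 patients". With an intracluster correlation of 0.01, an interperiod correlation of 0.008 and 31 hospitals, the required "size is 11,160 patients, or 180 patients per arm for each cluster". The registration target is 251 per arm per hospital, 15,562 in total.

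The final protocol (3.9 Sample size) describes that target as one "which will allow a 27% loss to follow-up". It adds that, if loss stays below 17%, the trial keeps 80% power for event rates up to 3% and 90% power for rates up to 2%. The SAP is more guarded. It treats 27% as a maximum reduction, expects actual loss to be lower, and says the surplus also covers uncertain event rates and correlations, unequal cluster sizes and hospitals dropping out.

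The final SAP (Main analyses) defines one difference per hospital and reads the treatment effect as the intercept "In a linear regression of cluster differences on treatment sequence". The same section, discussing early stopping, says that the investigators "increased the initial sample size by 27% above the minimum required" and uses this to argue that the loss of precision is mitigated.

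**The concern.** In the planned analysis the hospital is the unit. With 31 differences and two fitted parameters, the residual variance is estimated on 29 df, and ordinary regression inference would use a critical value of 2.045 instead of 1.960. Neither document mentions a t quantile, degrees of freedom or a small-sample addition. If the size was set on normal quantiles, the stated 11,160, the 27% loss allowance and the power at a 3% rate are each somewhat better than the described analysis would deliver.

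The 27% figure in Main analyses also looks wrong on its face, because it turns a tolerated reduction into an increase above the minimum. It matters a little because the SAP leans on this surplus when it discusses precision after early stopping.

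**Working it through.** **Inputs** (final SAP, Power and sample size; final protocol 3.9 and Table 1): rates 2.5% and 1.5%; difference 1 percentage point; one-sided alpha 0.025; ICC 0.01; IPC 0.008; k = 31 hospitals; m = patients per hospital-period; target m = 251.

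**1. Reproduce the plan.**
- Individual N per group = [1.960·√(2·0.02·0.98) + 1.282·√(0.025·0.975 + 0.015·0.985)]² / 0.01² = 4,116.8, rounded up to 4,117.
- m = n(1 − ICC) / (k − n(ICC − IPC)) = 4,117·0.99 / (31 − 4,117·0.002) = 4,075.83 / 22.766 = 179.03, rounded up to 180.
- 180 × 62 = 11,160. Every stated figure matches, with normal quantiles throughout. The same individual-N formula matches all 17 rows of Table 1.

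**2. Degrees of freedom.** 31 differences minus intercept and sequence term = 29.

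**3. Power on t(29).** SE² = [pₐ(1−pₐ) + p_c(1−p_c)]·[1 + (m−1)·0.01 − 0.008·m] / (31·m), with power taken from the noncentral t.
- 2% rate, m = 180: 0.03915 × 1.35 / 5,580, so SE = 0.308 points and 1/0.308 gives a ratio of 3.249. Normal power is Φ(3.249 − 1.960) = 90.1%; t(29) power is 88.1%.
- 3% rate (3.5% v 2.5%), m = 207: 0.05815 × 1.404 / 6,417, so SE = 0.357 points and the ratio is 2.803. Normal power is 80.1%; t(29) power is 77.3%.

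| Rate | m | Meaning | Normal | t(29) |
|---|---|---|---|---|
| 2% | 180 | stated requirement | 90.1% | 88.1% |
| 2% | 183 | 251 less 27% | 90.5% | 88.5% |
| 2% | 197 | first m to reach 90% on t | 91.9% | 90.0% |
| 2% | 208 | 251 less 17% | 92.8% | 91.1% |
| 2% | 251 | no loss | 95.4% | 94.1% |
| 3% | 207 | Table 1 requirement | 80.1% | 77.3% |
| 3% | 208 | 251 less 17% | 80.2% | 77.5% |
| 3% | 228 | first m to reach 80% on t | 82.6% | 80.0% |
| 3% | 251 | no loss | 85.0% | 82.5% |

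**4. Loss tolerance.**
- 90% at a 2% rate: 197 × 62 = 12,214, which is 12,214/11,160 = 1.094 times the stated size. Tolerable loss is 1 − 197/251 = 21.5%.
- 80% at a 3% rate: 228 × 62 = 14,136, against 12,834 in Table 1. Tolerable loss is 1 − 228/251 = 9.2%.

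**5. Robustness.** Using the pooled variance 2p(1−p) moves the required m by at most one patient and power by about 0.1 point. Dropping the sequence term (30 df) gives 88.2% at m = 180.

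**6. The surplus.** 15,562/11,160 = 1.394, so the target was 39% above the minimum. The tolerated reduction on the plan's own figures is 1 − 11,160/15,562 = 28.3%, which the documents give, slightly conservatively, as 27%.

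**The case against.** The strongest reply is that the effect is small and already covered. The headline shortfall is about 2 points of power, or 17 patients per hospital-period. In the plan's own formula, moving the interperiod correlation from 0.008 to 0.007 or 0.009 moves the requirement from 180 to 219 or 152, so the correction sits well inside the uncertainty the SAP acknowledges. The SAP does not reserve the surplus for loss alone, and it expected less than 27% loss. The target of 251 keeps 90% power on t(29) with up to 21.5% loss, and the protocol's 90% power at a 2% rate with loss below 17% survives (91.1%). All of this stands and sets the size of the point. It does not make the stated tolerances correct.

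A second reply is that 29 df is an inference, since no reference distribution is named, and that the final analysis is a composite of crossover and parallel estimators. That also stands. The t(29) figures describe the full-crossover design that was sized. The crossover part of the composite has fewer than 31 differences, so these figures must not be presented as its power.

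Third, recruitment ceased in December 2020, before the SAP was written, and the SAP reports what was used. The original calculation should therefore remain as the record.

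A reader might infer that the trial was underpowered, or that it needed more patients. The documents do not support that: the full target gives 94.1% at a 2% rate and 82.5% at 3%. Nor does correcting 27% to 39% undermine the precision argument by itself, because the slip understates the planned surplus. The weakness there is that early stopping means a planned surplus is not the number attained.

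**Conclusion.** The point holds as a modest correction to stated figures. For the full-crossover design on 29 df, power is 88% at 180 per hospital-period and also about 88% at 27% loss, not 90%. Power of 90% at a 2% rate is kept up to about 21% loss. Power of 80% at a 3% rate is kept up to about 9% loss and falls to about 77% at 17%. The gap is about 2 to 3 points of power, or 9 to 10% of the required number, and it arises only inside the loss ranges the protocol says it tolerates. The statement of 27% above the minimum is an arithmetic slip for 39%.

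This rests on the plan's rates and correlations, equal cluster sizes, and t-based inference for the regression described, which the plan does not state. It says nothing about whether the trial's conclusion is sound.

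**What to change.** - Keep 4,117, 180 and 11,160 as the record of the calculation made, and say that it used normal quantiles.
- Beside it, in the SAP's sample size section and the protocol's 3.9, restate the full-crossover design on 29 df: 88% power at 180 per hospital-period or at 27% loss; 90% up to about 21% loss; 80% at a 3% rate up to about 9% loss.
- In Main analyses, replace 27% with 39% above the minimum, or reword it as a tolerated reduction of 27%. Rest the precision argument on the number actually recruited, not on the planned surplus.
- Add a sentence that the composite analysis has fewer than 31 crossover differences, so these figures do not describe its power. It would help to name there the reference distribution used for the final interval.

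The cost is a few edited sentences with slightly less favourable numbers. No extra patients are needed, and the estimand and decision rule do not change.

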## **STATISTICAL ANALYSIS PLAN**

### **Patient Populations and Subgroups for Analyses**

The total patient population for CRISTAL comprises all patients undergoing HA or KA at participating institutions over the duration of the study, regardless of whether these patients were registered or eligible to receive the study drug (defined as population 5, see Figure 1).

Within this total population, the following populations will be used to form the basis of the analyses:

- Registered patients undergoing any form of HA or KA (including partial or revision surgery, for any indication) regardless of eligibility to receive the study drug (population 4)
- Registered patients undergoing any form of HA or KA (including partial or revision surgery, for any indication) who were eligible to receive the study drug (population 3)
- Registered patients undergoing elective primary THA or TKA (for any indication) who were eligible to receive the study drug (population 2)
- All registered patients undergoing elective primary THA or TKA for a recorded diagnosis of osteoarthritis (OA) who were eligible to receive the study drug (population 1)

These populations are represented diagrammatically in Figure 1.

**Figure 1.** Patient populations within CRISTAL

[figure not shown]

**Legend:**

Abbreviations: *HA* hip arthroplasty, *KA* knee arthroplasty, *THA* total hip arthroplasty, *TKA* total knee arthroplasty, *OA* osteoarthritis

† Study drug excluded for patients who already on long-term anticoagulation (specifically a novel oral anticoagulant – NOAC, warfarin or dual antiplatelet therapy – DAPT) and those who have a medical contraindication

Each outcome (primary and secondary) will be assessed for populations 1, 2, 3 and 4 listed in Figure 1. Mortality will be assessed for all populations (including population 5). The primary objective of the study as outlined in the published protocol [15], was the analysis of population 1 only (registered patients undergoing primary THA or TKA for a diagnosis of OA who are eligible to receive the study drug), as this was the focus of the sample size calculation. This population will remain the focus of the main analyses.

Population 1 was chosen as the focus of the main analysis as these patients represent the majority of patients undergoing HA or KA procedures and there are known differences in outcomes and co-morbidities with other diagnoses (e.g., fracture, tumour), which could confound the primary outcome [22].

For the primary end point of VTE, the following subgroup analyses will be conducted within the corresponding populations listed:

- Type of joint replacement: primary THA compared to primary TKA – population 1
- Bilateral arthroplasty: patients undergoing simultaneous bilateral arthroplasty compared to those who are not – population 1
- Revision arthroplasty: patients undergoing revision hip or knee arthroplasty compared to those undergoing primary arthroplasty – population 3
- Prior history of VTE: patients with a prior history of VTE compared to those without – population 1

### **Analysis principles**

Data will be analysed according to the intention-to-treat principle with clusters analysed according to assigned group allocation. Although hospital and patient protocol deviations will be recorded, no as-treated analyses will be performed, as there are no verified data available to determine whether individual patients received the assigned study drug for the full period, given the pragmatic nature of the trial. The timing of analyses will be stratified by follow-up time of the outcomes measured (90 days and 6 months). The difference in absolute risk for symptomatic VTE between each group and 95% confidence intervals (upper and lower) will be examined to determine if the non-inferiority margin is met.

Continuous variables will be summarised using standard measures of central tendency and dispersion, using either mean and standard deviation or median and interquartile range. Categorical variables will be summarised by frequencies and percentages.

Analyses will be performed using SAS version 9.4 (SAS Institute, Cary USA) and R (R Foundation for Statistical Computing Platform) version 4.0.2 or higher.

### **Interim analysis**

An interim analysis was not initially planned, as both treatments are considered standard practice for VTE prophylaxis in Australia and the trial is investigating an adverse event as the primary outcome. However, due to concerns of an increased adverse event rate (symptomatic VTE and death) in one of the prophylaxis groups, a Data Safety Monitoring

Board (DSMB) was convened one year into patient recruitment. The DSMB consisted of an orthopaedic surgeon, a haematologist and a statistician, all independent of the trial.

The DSMB were advised by the Trial Management Committee (TMC) to conduct an interim analysis. In conjunction with the DSMB (prior to the interim analysis), the TMC applied the Haybittle-Peto stopping rule of a two-sided significance of 0.001 for the primary outcome in the population 1 [23, 24]. This stopping rule was chosen as it does not require adjustment of the significance threshold for the final analysis and allows further interim analyses using the same threshold (if required).

After the first interim analysis (in September 2020), the DSMB recommended continuing the trial and performing a second interim analysis in November 2020. After reviewing the second interim analysis, the DSMB recommended ceasing patient recruitment as the stopping rule had been met. The study ceased recruiting patients in December 2020 and sites reverted to their usual VTE prophylaxis pathways.

### ***Methods used for Interim Analyses***

Interim analyses were conducted for VTE and mortality within 90 days for population 1. To account for unequal cluster sizes, incomplete crossover or clusters which had not yet crossed over, a composite analysis was designed. For clusters which had crossed over, including with partial completion of the second period, the cluster weighted estimator intended for the primary outcome was used. Harmonic mean weighting when there are unequal cluster sizes has been shown to improve precision and 95% confidence interval coverage compared with unweighted or inverse variance estimates [25, 26]. Clusters which had not crossed over were analysed using the cluster period summaries, weighted by cluster size, in a parallel design approach, i.e., as if it were a cluster randomised trial without crossover. Estimates for the two approaches were combined using inverse variance weights to provide a final estimate. Confidence intervals were constructed using the Haybittle-Peto boundary of 0.001.

### **Data integrity**

Integrity of data will be checked prior to conducting the final analysis. The data set will be checked for errors, omissions and double data entry. These will be resolved prior to commencing the analysis in consultation with the data management plan [15].

### **Blinding**

The DSMB were blinded to treatment allocation (groups in the interim analyses were labelled A and B). All researchers involved in the preparation of this analysis plan will have no access to trial data broken down by treatment allocation for the final statistical analysis. Once data integrity checks have been conducted, a blind review to quantify missing data of the entire dataset will be conducted and any final amendments to the statistical analysis plan will be made before the database is locked. During analysis and interpretation, group allocation will be masked by dummy group names and the true allocation will be unmasked only after the final statistical report has been completed and interpretation has been agreed to by the writing group and minuted.

